### Sample size calculation

A sample size was calculated to test the alternative hypothesis that FECPAK^G2^, Mini-FLOTAC and single Kato-Katz thick smear provide equivalent drug efficacy results measured by ERRs compared to a duplicate Kato-Katz thick smear. Given the differences in drug efficacy of ALB across the STH species [15, 21] (*Ascaris*: ~99%, hookworms: ~96%, *Trichuris*: ~65%), a level of equivalence that is acceptable for *Trichuris* may not be acceptable for *Ascaris*. Therefore, a species-specific level of equivalence was used. For *Ascaris* the level of equivalence was set at 2.5-point percentage, for hookworms and *Trichuris* the level of equivalence was set at 5.0 and 10 point percentage, respectively. Both type I and II errors were set at 0.05.

To calculate the corresponding sample size for each of the STH species, we performed a simulation study. This simulation study considered (i) variation in ERR and baseline FECs across and within STH species, (ii) variation in FECs introduced by the egg counting process, (iii) the paired ERR results across egg count methods, and (iv) a post-hoc correction for a pair-wise comparison. Based on the simulation, at least 110, 100 and 12 complete cases are required for *Trichuris*, hookworm and *Ascaris*, respectively. A detailed description of the sample size calculation is available in the supplementary information (S1 Info).

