#### Pyrosequencing

In two subsets of the DNA samples, we will apply a previously described pyrosequencing protocol [30, 52] to determine frequency of mutant SNPs in the three codons of the ß-tubulin associated with BZ resistance. The first subset will consist only of baseline DNA samples, and will be used to assess the association between drug pressure history and the corresponding frequency of mutant SNPs linked to BZ resistance. Per study site, 60 baseline DNA samples positive for each STH species (*Ascaris*, *Trichuris* and hookworm) will be randomly selected from the available baseline DNA samples. To avoid these samples representing one school or one level of individual response to ALB, selection of the samples will be proportionately to the total number of cases per school and individual drug response (Table 3).

**Table 3 pntd.0006912.t003:** Classification of the individual response to a single oral dose 400 mg ALB against STH based on the individual egg reduction rate (iERR).

STH	Cured	Responder	Poor responder	Non-responder
***Ascaris***	iERR = 100%	iERR ≥ 95%	85% ≤ iERR < 95%	iERR < 85%
***Trichuris***	iERR = 100%	iERR ≥ 50%	40% ≤ iERR < 50%	iERR < 40%
**Hookworms**	iERR = 100%	iERR ≥ 90%	80% ≤ iERR < 90%	iERR < 80%

We will use a second set of DNA samples to assess the association between individual responses to ALB by pyrosequencing the ß-tubulin gene. At each site, samples from at least 30 participants who were cured (baseline samples only) and from at least 30 participants who were still excreting eggs at follow-up (both baseline and follow-up samples) will be selected for each STH species separately. Participants which still excreted eggs will be stratified, into ‘responders’, ‘poor responders’ and ‘non-responders’. This stratification will be based on WHO thresholds used for classifying the efficacy into ‘satisfactory’ (‘responders’), ‘doubtful’ (‘poor responders’) and ‘reduced’ (‘non-responders’) [27] (Table 3). A total of 10 participants will be randomly selected for each stratum. Total DNA will be extracted from these stool samples and sent for pyrosequencing at McGill University (Canada).

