### Assess associations between frequency of SNPs linked to BZ resistance measured by pyrosequencing and history of drug pressure and drug efficacy

To assess the association between mutant SNPs linked to BZ resistance and history of drug pressure, a permutation test will be applied to evaluate differences in frequency of mutant SNPs linked to BZ in the baseline samples across the study sites. Tukey’s method will be applied for pair-wise comparisons between the study sites.

To assess the association between mutant SNPs linked to BZ resistance and drug efficacy, a permutation test will be applied to evaluate any difference in frequency of mutant SNPs linked to BZ across the four levels of individual response to ALB (Table 3). Tukey’s method will be applied for pair-wise comparisons between the four levels of individual response.

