By standardizing the drug efficacy trials (e.g., egg count method, follow-up period, anthelmintic drug and statistical analysis) and strategically selecting the study sites (varying drug pressure history, and hence possibly differences in drug efficacy), we hope to provide complementary insights into SNPs in the β-tubulin gene as a marker for BZ resistance in human STHs. If these SNPs play a role in AR, we expect an increase in frequency in mutant SNPs in STHs as a function of increased drug pressure history and decreased individual response to treatment. However, this molecular part of the study may face some challenges, which may impede a straightforward interpretation of the results. First, if the expected trends in SNPs are not detected, it is not possible to completely exclude them as a marker for BZ resistance. Furthermore, it could also indicate that resistance to BZ has not yet emerged, which would also jeopardize any downstream objectives (e.g. comparison of pyrosequencing and LAMP for the assessment of SNPs linked to BZ resistance and assessing pooling samples as a cost-saving strategy to determine the frequency of SNPs linked to BZ resistance). It is also important to note that any observed trends would only suggest an association rather than causal relationship. Second, it remains unclear whether we will be able to select the number of cases per level of individual response for each of the different STH species. Finally, the classification of the individual response is based on the outcome of imperfect tests (sub-optimal sensitivity), further complicating the interpretation.

To conclude, the combined results of this study are expected to answer a number of outstanding questions with regards to how to best monitor drug efficacy and measure AR in populations that are being subjected to PC for STH infections. The results could be translated into novel recommendations for the scientific community on what is the best diagnostic method to assess drug efficacy in ongoing control programs and will create the basis to set up a robust surveillance system.

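### The SNP-versus-response test ignores the order of the four response levels although the protocol predicts a rise; adding an ordered-alternative permutation test as the main test would be a cheap gain in power

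*Protocol article*

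**What the plan says.** The statistical section on SNPs, drug pressure and drug efficacy (Protocol article) sets a permutation test to "evaluate any difference in frequency of mutant SNPs linked to BZ across the four levels of individual response to ALB". It adds that Tukey's "method will be applied for pair-wise comparisons between the four levels of individual response".

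The levels come from Table 3 in the Pyrosequencing section, titled "Classification of the individual response to a single oral dose 400 mg ALB against STH based on the individual egg reduction rate (iERR"). Cured, responder, poor responder and non-responder are successive bands of that one scale.

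The same section plans, per site and species, "samples from at least 30 participants who were cured (baseline samples only"), plus at least 30 participants still excreting eggs, split by response: "A total of 10 participants will be randomly selected for each stratum".

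The Discussion states the hypothesis: "we expect an increase in frequency in mutant SNPs in STHs as a function of increased drug pressure history and decreased individual response to treatment". It also concedes that "it remains unclear whether we will be able to select the number of cases per level of individual response".

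**The concern.** The hypothesis is directional over an ordered scale, but the test looks for any difference among four unlabelled groups. An omnibus comparison spreads its three degrees of freedom over all patterns, including ones that the hypothesis excludes. All-pairs Tukey contrasts also ignore the order. Three of the six pairs compare 10 with 10 children per site and species, and the other three compare 30 with 10.

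Two things follow. If SNP frequency does rise as response falls, the planned test is less likely to detect it than one built for ordered alternatives. A significant omnibus result also need not support the hypothesis, because a peak confined to responders would produce one too. Both matter because the uncured strata are small and may not be filled. The Discussion also says that failing to see the expected trends cannot fully rule the SNPs out as a marker, so an avoidable false negative would leave the question open.

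**Working it through.** **No figure to reproduce.** The article gives no power, effect size, standard deviation or shape of the rise for this objective. "Both type I and II errors were set at 0.05" belongs to the ERR equivalence sample size.

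**Inputs.**
- Group sizes 30/10/10/10 per site and species: Pyrosequencing section, with the cured minimum taken as the actual number.
- Order cured < responder < poor responder < non-responder in predicted SNP frequency: Table 3 and Discussion.
- Assumptions: two-sided 5%; normal group means with known common SD; six monotone shapes.

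**Planned test.** The omnibus statistic is Σ nᵢ(ȳᵢ − ȳ)²/σ², referred to chi-square with 3 df (critical value 7.81). Its power depends on λ = Σ nᵢ(μᵢ − μ̄)²/σ². Power of 80% needs λ ≈ 10.90, and 50% needs λ ≈ 5.76.

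For example, take a linear rise with scores 0, 1, 2, 3.
- Weighted mean: (0 + 10 + 20 + 30)/60 = 1.
- Sum of squares: 30×1 + 10×0 + 10×1 + 10×4 = 80.
- Difference between extreme levels at 80% power: 3×√(10.90/80) ≈ 1.11 SD.

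If only non-responders are raised, the sum of squares is 10×(1 − 1/6) ≈ 8.33, and the difference is √(10.90/8.33) ≈ 1.14 SD.

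**Ordered test.** Fit increasing and decreasing isotonic means by weighted least squares. Take the larger of the two values of Σ nᵢ(μ̂ᵢ − ȳ)²/σ². The simulated two-sided 5% critical value is 5.65.

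**Isotonic power (Monte Carlo; repeat runs agree within about 0.3 points), with effects scaled so that the planned test has the stated power:**

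| Shape | Planned 50% | Gain | Planned 80% | Gain |
|---|---|---|---|---|
| Linear | 63.2 | 13.2 | 88.8 | 8.8 |
| Accelerating | 62.5 | 12.5 | 88.4 | 8.4 |
| Concave | 61.6 | 11.6 | 87.9 | 7.9 |
| Poor and non-responders raised | 59.1 | 9.1 | 86.5 | 6.5 |
| All uncured raised | 57.8 | 7.8 | 85.8 | 5.8 |
| Non-responders only | 57.6 | 7.6 | 85.6 | 5.6 |

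At other levels of planned power the gain is:
- 10%: 1.6-3.4 points
- 20%: 4-8 points
- 95%: 1.9-2.9 points
- 99%: under 1 point

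Pooling four sites (120/40/40/40) keeps the same proportions. For a given base power the gains are therefore unchanged under this model.

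**Skewed data.** In permutation simulations at 30/10/10/10 with zero-inflated skewed frequencies, the isotonic statistic gained 9-12 points for graded or late-step shapes. It gained about 2-6 when all uncured differ from cured (38.5% to 40.5%; 47.9% to 53.7%). The planned test's null rejection rate was 5.3%.

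**Why not a linear-score trend.** It does better for a linear rise (80% to 91%) but loses if only non-responders differ (80% to 73%), which is still a monotone pattern.

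**Non-monotone patterns, planned test at 80%.**
- Peak in responders only: isotonic power about 30%.
- Cured one step above responders (pattern 1, 0, 1, 2): 66%.
- Pattern 1, 0, 0, 2: 60%.

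**The case against.** The planned test is not wrong. It holds its type I error, and testing for any difference does not contradict a directional expectation; it is only less sharp. A condensed article may leave the exact permutation statistic to an analysis plan that is not shown. This stands, and it makes the point an improvement rather than an error. It does not remove the point, because the article itself names the alternative being tested.

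An open test can also be defended for exploratory marker work. The Discussion says that the classification rests on tests with imperfect sensitivity, so the boundary between cured and responder is insecure. If cured children sit above responders, the isotonic test loses 14-20 points (80% to 66% or 60%). This stands, and it is why the omnibus test should be kept.

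The Tukey contrasts show direction and where levels separate, so a wrong-way pattern would be visible. A reader might infer that the plan would count any significant difference as validating the marker. The article does not say that: the Discussion states the expected direction and limits any finding to association.

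**Conclusion.** The planned analysis is valid but inefficient for the hypothesis that the protocol states. With 30/10/10/10 children, normal group means and two-sided 5%, the isotonic test gains about 6-9 points at 80% base power, 8-13 at 50% and 4-8 at 20%, for all six monotone shapes. Towards either extreme of power the gain shrinks to a few points or less.

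A reader might take these ranges as a known loss of power. The article does not support that: it gives no effect size, SD or shape, and it allows that resistance may not yet have emerged, in which case power could be very low under either test. Nor is the power lost for good. The cured and uncured totals are minimums rather than fixed numbers, and an ordered analysis can be run on the same data. What would be lost is the standing of a pre-specified test.

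**What to change.** In the section on associations between SNP frequency, drug pressure and drug efficacy:

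1. Name as the main test of the response association a two-sided isotonic (ordered-alternative) permutation test over cured < responder < poor responder < non-responder, with labels permuted within site.
2. Keep the omnibus permutation test and the Tukey comparisons as secondary analyses.
3. State that the result supports the SNPs as a marker only if the trend runs in the direction given in the Discussion.

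The cost is a few sentences and a few lines of R within the permutation framework already planned, with no new samples or assays. The downside is lower power for the main test if the pattern is not monotone, and the retained omnibus test covers that case.

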### General design of the field trials

A series of drug efficacy trials will be performed in four STH endemic countries (Brazil, Ethiopia, Lao PDR and Tanzania). These trials will be designed to assess the efficacy of a single oral dose of 400 mg ALB against STH infections in SAC by a variety of stool-based diagnostic methods. At the start of each trial, schools will be visited by the local principal investigator (PI) and a team of field officers, who will explain the planned trial and sampling method to the parents and teachers and the children. At baseline, SAC will be asked to provide a fresh stool sample. All children that meet all inclusion criteria and none of the exclusion criteria (see Table 1) will be enrolled in the study. They will be treated with a single oral dose of 400 mg ALB under supervision. The ALB to be used in the different studies is manufactured by GlaxoSmithKline and donated to WHO and originates from the same production batch (Batch Nr: 335726). All collected stool samples will be processed to determine the fecal egg counts (FECs; expressed in eggs per gram of stool (EPG)) for each STH using Kato-Katz thick smear (single and duplicate), Mini-FLOTAC and FECPAK^G2^. During baseline evaluation, only stool samples found to contain at least 13 eggs on duplicate Kato-Katz or at least 15 eggs on Mini-FLOTAC for at least one of the three STHs will be preserved for further molecular analysis. Fourteen to 21 days after drug administration, a second stool sample will be collected from all the children that were excreting eggs of any STH at baseline based on Kato-Katz thick smear and Mini-FLOTAC. Stool samples will be examined by Kato-Katz thick smear (single and duplicate), Mini-FLOTAC and FECPAK^G2^. All follow-up samples will be preserved for further molecular analysis. To gain insights into the operational costs for assessing drug efficacy, the time to process stool with Kato-Katz thick smear, Mini-FLOTAC and FECPAK^G2^, and the time needed to enter data and to draft reports will be assessed. The different steps of the trials are schematized in Fig 1.

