### Egg counting methods

#### Kato-Katz thick smear

Kato-Katz thick smears will be prepared on microscope slides using a square template with a hole of 6 mm diameter and 1.5 mm deep, which is assumed to sample 41.7 mg of stool [61]. Two Kato-Katz thick smears will be prepared per sample (slide A and B) and to avoid clearing of hookworm eggs, all slides will be examined within 30–60 min for the presence of STH eggs. The number *A*. *lumbricoides*, *T*. *trichiura* and hookworm eggs will be counted and recorded per slide. Slide A will represent a single Kato-Katz thick smear. For the duplicate Kato-Katz thick smear, the egg counts of slide A and B are added and multiplied by 12 to obtain the FEC. A detailed SOP on how the duplicate Kato-Katz thick smears will be processed is provided in S3 Info.

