### DNA-based methods

#### Stool preservation and DNA extraction

After performing the egg counting methods, stool samples will be preserved. At baseline, only those samples in which a sufficient number of eggs are counted for at least one STH species will be preserved (duplicate Kato-Katz thick smear: 13 eggs; Mini-FLOTAC: 15 eggs). At follow-up, all samples will be preserved, and this regardless of the number of STH eggs found. For each sample, 2 subsamples of 0.5 g will be preserved in 1 ml of absolute ethanol. A detailed SOP on sample preservation is provided in the supplementary information (S7 Info). Preserved samples will be stored in sample boxes at room temperature and shipped to Belgium for DNA extraction and subsequent molecular analysis. The DNA extraction protocol will be run on the automated QiaSymphony using a preceding mechanical lysis step by means of bead beating. This DNA protocol maximizes STH DNA yield from stool (Ayana et al, in preparation). DNA extraction will be performed at Ghent University (Belgium) and Elizabeth Tweesteden Hospital (The Netherlands). S8 Info provides a detailed SOP on DNA extraction.

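### Group efficacy cut-offs applied to single children with low egg counts make response class depend on baseline count, clearly for Ascaris, and the SNP test across those classes fixes neither visit nor site

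*Protocol article*

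**What the plan says.** **Classes.** Table 3 (Pyrosequencing) sorts children by individual egg reduction rate (iERR) into cured, responder, poor responder and non-responder. On the source of the cut-offs the section says: "This stratification will be based on WHO thresholds used for classifying the efficacy into" satisfactory, doubtful and reduced. Table 4 (equivalence of egg reduction rates) applies the same numbers to the group ERR, which is computed from arithmetic means: 95/85% for Ascaris, 90/80% for hookworms, 50/40% for Trichuris.

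**Which baseline samples exist.** General design of the field trials keeps baseline stool for molecular work if it has "at least 13 eggs on duplicate Kato-Katz or at least 15 eggs on Mini-FLOTAC for at least one of the three STHs". Stool preservation and DNA extraction repeats this: "At baseline, only those samples in which a sufficient number of eggs are counted for at least one STH species will be preserved". Neither section sets a minimum for the species that is later classed.

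**Second pyrosequencing subset.** Per site and species it takes "samples from at least 30 participants who were cured (baseline samples only") and samples "from at least 30 participants who were still excreting eggs at follow-up (both baseline and follow-up samples"). The uncured are split into three strata of 10.

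**Tests.** The analysis section limits the drug-pressure comparison to baseline samples. The next paragraph, on drug response, compares SNP frequency "across the four levels of individual response to ALB" by a permutation test with Tukey comparisons. It names no visit and no stratification by site.

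**The concern.** A cut-off meant for a mean over many children is stable because counting noise averages out. In one child with 13 eggs, each egg is worth 100/13 = 7.7 percentage points, which nearly spans the 10-point poor-responder band for Ascaris. Part of the classification then records how many eggs were counted at baseline and not how the worms responded. That dilutes any true link between SNP frequency and response.

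The unstated visit is a separate matter. Post-treatment DNA exists only for uncured children. If it entered the class test, the cured and uncured groups would differ in visit as well as in response. The Introduction to work package 1 reports, from small earlier studies, that resistance-associated mutations rose after treatment in *T. trichiura*. This comparison is one of the two on which the plan rests its validation of the SNPs as a resistance marker.

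**Working it through.** **Plan's own figures.** 3 strata × 10 = 30 uncured children per site and species, as stated. The Kato-Katz factor is 1/(2 × 0.0417 g) = 11.99, which agrees with: "the egg counts of slide A and B are added and multiplied by 12 to obtain the FEC". So 13 eggs is 13 × 12 = 156 EPG.

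**Step 1: reachable classes (arithmetic only).** iERR = 100% × (1 − follow-up eggs / baseline eggs).

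| Species | Baseline eggs | Eggs left | iERR | Class |
|---|---|---|---|---|
| Ascaris | 13 | 1 | 92.3% | poor |
| Ascaris | 15 | 1 | 93.3% | poor |
| Ascaris | 19 | 1 | 94.7% | poor |
| Ascaris | 20 | 1 | 95.0% | responder |
| Ascaris | 13 | 2 | 84.6% | non-responder |
| Hookworm | 13 | 1 / 2 / 3 | 92.3 / 84.6 / 76.9% | responder / poor / non-responder |
| Hookworm | 10 | 1 | 90.0% | responder |
| Hookworm | 4 | 1 | 75.0% | non-responder |
| Trichuris | 13 | 6 / 7 / 8 | 53.8 / 46.2 / 38.5% | responder / poor / non-responder |

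An uncured child needs at least 20 Ascaris or 10 hookworm eggs before the responder class can be reached. The hookworm row with 4 eggs can occur in a child who qualified on another species.

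**Step 2: how often noise alone sets the class.** Every child is given the same true efficacy, from Sample size calculation (Ascaris 99%, hookworm 96%, Trichuris 65%). With baseline count b taken as fixed, the follow-up count is Poisson with mean b(1 − ERR).

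- Ascaris, b = 13: mean 0.13, P(uncured) = 1 − e^(−0.13) = 12%. All of these are labelled poor or non-responder. At b = 20 the share is 10%, at 50 it is 4%, at 200 it is 0%.
- Hookworm, b = 13: mean 0.52, P(uncured) = 40.5%, of whom 24% are labelled poor or non-responder. At b = 50 it is 2%, at 200 it is 0%.
- Trichuris, b = 13: mean 4.55, 18% of the uncured. At b = 50 it is 3%.

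**Step 3: does the direction survive other count models?** Here the baseline count also varies about the child's mean, and only children with at least 13 eggs are kept. The table gives the share of uncured children labelled poor or non-responder at mean counts 13 / 50 / 200.

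| Species | Poisson | Negative binomial, k = 1 |
|---|---|---|
| Ascaris | 93 / 5 / 0% | 46 / 25 / 19% |
| Hookworm | 22 / 5 / 0% | 18 / 24 / 27% |
| Trichuris | 8 / 8 / 0.3% | 13 / 30 / 38% |

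The excess at low counts holds under both models for Ascaris only. With strong overdispersion it reverses for the other two species.

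**Step 4: visit and site.** With full quotas, four sites give 4 × 30 = 120 cured samples (none from follow-up) and 4 × 30 × 2 = 240 uncured samples (half from follow-up) per species. Simulated type I error of an omnibus permutation test across the four classes, with no true class effect (nominal 5%, 400 replicates, so about ±1.1 points standard error at 5%):

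| Scenario | Rejection |
|---|---|
| Baseline only, full quotas, sites alike | 3.0% |
| Visits pooled, no visit effect | 11.5% |
| Visits pooled, follow-up frequency 0.05 higher | 48% |
| Visits pooled, follow-up frequency 0.10 higher | 96% |
| Baseline only, sites differ, full quotas, unstratified | 1.3% |
| Baseline only, sites differ, unfilled quotas, unstratified | 28% |
| Same, permuted within site | 4.3% |

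The documents give no SNP frequencies, so these inputs are assumptions: SD 0.10, within-child correlation 0.5, site means 0.05, 0.05, 0.10 and 0.20 where sites differ, and unfilled quotas of 2, 3, 5, 10 (poor) and 2, 2, 4, 10 (non-responder) over the four sites.

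**The case against.** A reader might infer that the plan mixes visits and permutes children across sites. The text does not say so. It leaves both open, and taking both visits from uncured children fits a sensible paired comparison. An article may leave such detail to the full analysis plan. That stands as far as the wording goes. What remains is that the article itself fixes an unequal sampling frame, names baseline for one SNP test, and drops it for the next.

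Site is balanced by design, since selection is made at each site with 10 per stratum. With full quotas the simulation shows no inflation (1.3%). This stands, so site is a risk only if quotas fail, and the Discussion says that is unclear.

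The Discussion also concedes that individual classification rests on imperfect tests. It names sub-optimal sensitivity only, not dependence on baseline count. It is fair to add that 13 eggs is the floor, that no count distribution is given, and that the plan does not say which egg-count method yields iERR. Noise in the classes creates a false association only if SNP frequency itself varies with baseline count. Otherwise it dilutes.

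The omnibus test with Tukey comparisons is not an error. An ordered trend test is an option, and any gain in power depends on an assumed gradient.

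**Conclusion.** Two points hold. First, Table 3 puts group cut-offs on single-child counts without a minimum for the species being classed. For Ascaris, an uncured child with 13 to 19 eggs cannot be a responder. That is arithmetic and needs no model. For hookworm and Trichuris the effect is smaller and depends on the count model, except that a co-infected child with 1 to 4 hookworm eggs and one left is always a non-responder. The documents do not support a general claim that response class stands in for baseline count in all three species.

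Second, the drug-response SNP test should name its visit. Pooling visits would bias the comparison of cured with uncured children, by an amount that depends on the assumed SNP frequencies. Stratifying by site is a safeguard against unfilled quotas and does not correct a flaw in the selection as planned. The main expected harm from the first point is a diluted association. The harm from pooled visits would be a false one.

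**What to change.** 1. For the second pyrosequencing subset, require a minimum baseline count of the species being classed so that every class can be reached: at least 20 Ascaris or 10 hookworm eggs. Alternatively, keep all children and adjust the class comparison for baseline FEC. A minimum does not remove counting noise: at exactly 20 Ascaris eggs about 10% of uncured children would still be mislabelled under the Poisson model.
2. Run the class test on baseline SNP frequency only, one value per child.
3. Analyse the change from baseline to follow-up in uncured children as a separate paired test.
4. Permute within site.

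These are changes to selection rules and analysis wording, to be made before DNA is selected. The cost is that some low-count children become ineligible, which may make the poor-responder and non-responder quotas harder to fill. How many cannot be said from the documents. If that loss looks too large, adjustment for baseline FEC avoids it.
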